### Outcome measurement

#### Primary outcome

The primary outcome will be the mean change in HAMD-17 score from baseline to week 12. The HAMD-17 is a questionnaire designed to evaluate the symptoms of individuals diagnosed with depression, which is an observer-rated questionnaire consisting of 17 items (15). The scale uses either a 3-point or 5-point rating system and has demonstrated strong reliability and validity, making it a widely used tool in both research and clinical settings. A higher overall score indicates a higher level of depression, with scores ranging from 0 to 54; scores of 0–6 indicate a normal person without depression; 7–16, likely or suspected to have depression; 17–24, mild to moderate depression; ≥25, severe depression. This outcome data will be collected at baseline, during the treatment phase (at 4, 8, and 12 weeks), and at the 16-, 24-, and 36-week follow-ups.

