#### Secondary outcome

The depression recovery rate is the percentage of patients with a HAMD-17 score ≤7 after 12 weeks of treatment. The recovery rate refers to the percentage of individuals who have successfully overcome or managed their symptoms of depression, and will be collected at 12 weeks.The depression remission rate is the percentage of patients between 8 ≤ HAMD-17 ≤ 12 after 12 weeks of treatment. The remission rate refers to the percentage of individuals who have achieved a significant reduction in symptoms of depression, which may involve some residual symptoms but not at levels that would meet the diagnostic criteria for depression. This outcome data will be collected at 12 weeks.The Patient Health Questionnaire-9 (PHQ-9) is an essential self-administered depression screening and diagnostic tool for screening and assessing patients’ depressive status (16–18). It consists of nine items that are easily and effectively used to understand a subject’s depression in the past two weeks. The total scores might be anywhere from 0 (no depression symptoms at all) to 27 (daily occurrence of all symptoms). The higher the total score indicates, the more severe the depression. This outcome data will be collected at baseline, during the treatment phase (at 4, 8, and 12 weeks) and at the 16-, 24-, and 36-week follow-ups.The 36-Item Short Form Health Survey (SF-36) is one of the most widely used quality-of-life assessment scales with good reliability and validity (19). It provides a comprehensive overview of the participants’ quality of life in eight dimensions: physiological functioning, physical functioning, somatic pain, general health status, energy, social functioning, emotional functioning, and mental health. Higher scores represent a better health status. This outcome data will be collected at baseline, and during the treatment phase (at 4, 8, and 12 weeks).The dose and frequency of drugs will be recorded by participants based on actual daily dosing from baseline to the 6-month follow-up period.

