### Statistical analysis

Analyses will be conducted on the intention-to-treat (ITT) population, which comprises all qualified participants who meet the inclusion criteria, have received the intervention at least once, and have provided at least one outcome assessment. In statistical analysis, any missing primary outcome data will be replaced by the last observed data point, in accordance with the ITT principle. Additionally, a Per-Protocol Set (PPS) analysis will be employed to assess those participants who completed the trial without significant protocol violations. Data analysis for this study will be performed using the statistical software SPSS V.24.0. Descriptive statistical analysis will be used for all demographic and clinical characteristics of subjects, such as sex, age, and weight. We will validate the homogeneity of demographic characteristics and examine the variables between the two groups. The number of patients who change their medication dosage will also be counted, and the variations between the two groups and within each group will be analyzed. If measurement data follows a normal distribution and has homogeneity of variance, the data values will be reported as mean ± standard deviation (MD ± SD). Covariance analysis will be used to compare the data across different groups. If the data does not adhere to the assumed normal distribution, the median values (P25, P75) will be used to characterize it. The Mann-Whitney U nonparametric test will be used to compare between groups. The mean ± standard deviation will be used for the description of the continuous variables. Qualitative data will be expressed in terms of frequency and percentage. The student’s t-test will be utilized for comparing measurement data between two groups from baseline to the 6-month follow-up, while the rank sum test will be used for ranked data, and the χ2 test will be used for analyzing categorical data. A paired t-test was used for comparisons before and after treatment within a group, and an analysis of variance was used for comparisons among different groups. Repeated-measurement analysis of variance was used to compare groups at multiple observation points. A significance level of 2.5% will be used for all statistical analyses, using two-tailed testing. Subgroup analysis will be conducted to examine differences between different genders and across various age brackets.

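### Recovery is tested without the baseline HAMD-17 that is collected, and for PHQ-9 and SF-36 an unadjusted t-test competes with covariance analysis: a modest, avoidable loss of precision on secondary outcomes, not bias

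*Protocol article*

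**What the plan says.** The methods are in the Statistical analysis section of the protocol article.

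- **Categorical outcomes.** The chi-square "test will be used for analyzing categorical data". No other between-group method is given for them. The Secondary outcome section defines recovery as the "percentage of patients with a HAMD-17 score ≤7 after 12 weeks of treatment", and remission as a score of 8 to 12 at the same visit, so both fall under this test.
- **Measurement data.** Four parametric methods appear. For normal data with equal variances, "Covariance analysis will be used to compare the data across different groups" (otherwise Mann-Whitney U). Later, Student's "t-test will be utilized for comparing measurement data between two groups from baseline to the 6-month follow-up". Analysis of variance is then named for comparisons among groups, and finally "Repeated-measurement analysis of variance was used to compare groups at multiple observation points". None is tied to PHQ-9 or SF-36 by name, none is called decisive, and the covariance analysis has no stated covariate.
- **Baselines.** On HAMD-17 the Primary outcome section says "This outcome data will be collected at baseline, during the treatment phase (at 4, 8, and 12 weeks), and at the 16-, 24-, and 36-week" visits. PHQ-9 has the same schedule, and SF-36 is taken at baseline and at weeks 4, 8 and 12.

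**The concern.** Recovery is a fixed cut on the scale that also governs entry. A patient who enters at 17 must fall 17 - 7 = 10 points to count as recovered, and one who enters at 24 must fall 24 - 7 = 17. Entry severity is therefore a natural predictor of recovery. It is recorded before treatment, and the chi-square test leaves it out. Recovery is also the secondary result that clinicians will read most easily.

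For PHQ-9 and SF-36, the entry criteria do not restrict the baseline directly, so it may predict the later score better. A t-test on final scores ignores it, and a t-test on change uses it inefficiently. Because the section names an adjusted and an unadjusted method for the same data, the choice could be made after the results are seen.

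**Working it through.** The plan gives no figure for these comparisons: no baseline to outcome correlation, no expected recovery rate and no week-12 SD. The sample size calculation concerns the primary outcome only. The sizes below therefore rest on stated assumptions.

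**Recovery: inputs**
- Entry HAMD-17 of 17-24 (Inclusion criteria). If uniform over these eight values (assumed), the mean is 20.5 and the SD 2.29.
- Week-12 mean: 20.5 - 11.3 = 9.2, using the fall in the drug group from the Sample size calculation section.
- Week-12 SD of 6 (assumed).
- 102 per arm (Sample size calculation).

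**Recovery: precision gain.** The raw risk difference was compared with the risk difference standardised over baseline from a logistic model, in two separate simulations of 4,000 trials per setting.

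| Correlation r | Variance reduction, first simulation | Variance reduction, second simulation | Implied slope r x 6 / 2.29 |
|---|---|---|---|
| 0.2 | 2.5% | 1.4% | 0.52 |
| 0.3 | 5.6% | 5.2% | 0.79 |
| 0.4 | 10% | 8.2% | 1.05 |
| 0.5 | 17% | 16.3% | 1.31 |

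With 81 per arm the second simulation gives 2.1%, 5.1%, 8.8% and 15.6%.

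The last column shows which rows are plausible. A slope above 1 means that entry differences do not shrink but widen over 12 weeks of treatment. That makes r = 0.4-0.5 unlikely and r = 0.2-0.3 the sensible main case. A larger week-12 SD strengthens this. If the 11.5 that the plan gives for the fall in HAMD-17 were carried over to the week-12 score, r = 0.3 would need a slope of 0.3 x 11.5 / 2.29 = 1.51.

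In standard errors, the raw risk difference has an SE of about 6.9 percentage points. At r = 0.2 this becomes 6.9 x sqrt(1 - 0.025) = 6.8, and at r = 0.3 it becomes 6.9 x sqrt(1 - 0.056) = 6.7.

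**Recovery: chance imbalance.** The SE of the difference in mean baseline is 2.29 x sqrt(2/102) = 0.32 points. Near the cut of 7, the assumed normal density is about 0.062 per point. An imbalance of one SE then moves the recovery difference by 0.32 x 0.52 x 0.062 = 1.0 percentage point at r = 0.2, and by 0.32 x 0.79 x 0.062 = 1.6 points at r = 0.3.

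**Recovery: validity and power.** A further simulation used 81 per group, two-sided 0.025, assumed recovery of 35% against 60%, and 1,500 runs per setting. The correlation here is on the latent scale.

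| Correlation | Power, chi-square | Power, adjusted logistic | Null rejection, chi-square / adjusted |
|---|---|---|---|
| 0.2 | 0.82 | 0.84 | 0.025 / 0.025 |
| 0.3 | 0.83 | 0.86 | 0.021 / 0.021 |
| 0.5 | 0.82 | 0.90 | 0.024 / 0.026 |

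Both tests keep their level.

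**PHQ-9 and SF-36.** With correlation r, the variance of the covariance-adjusted estimate is 1 - r^2 times that of a t-test on final scores, and (1 + r)/2 times that of a t-test on change.
- r = 0.3: 1 - 0.09 = 0.91 (9% less) and 1.3/2 = 0.65 (35% less).
- r = 0.5: 1 - 0.25 = 0.75 (25% less) and 1.5/2 = 0.75 (25% less).

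Against final scores, 81 adjusted patients per group are worth 81/0.91 = 89 or 81/0.75 = 108 under the t-test. These gains apply only if the t-test is the analysis carried out.

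**The case against.** The strongest reply is that nothing stated is wrong. In a 1:1 randomized trial the chi-square test is a valid comparison of marginal recovery, and the simulated null rejection rates bear this out. Chance imbalance is already part of the standard error. A shift of 1.0-1.6 percentage points is small beside a sampling SE of about 6.9. All of this stands, and it makes the point one of efficiency. A reader might infer that the unadjusted tests bias the secondary results, and the documents do not support that.

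A reader might also infer that PHQ-9 and SF-36 are settled as unadjusted. They are not. The same section prescribes covariance analysis for normal data and lists two further methods, so the t-test is one of several candidates. What stands is that the section permits an unadjusted test and does not say that the adjusted one decides.

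A third tempting reading is that recovery loses 10% or more of its precision. That needs r of 0.4 or higher, which the narrow entry range makes unlikely.

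Finally, covariate lists are often left to the analysis plan, and this is a condensed article. The missing list is therefore not the finding. The point rests on the methods stated: chi-square as the only named test for categorical data, and competing tests for the same measurement data.

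**Conclusion.** The point holds as a low-priority improvement to secondary analyses. As written, the recovery comparison uses no baseline, and the between-group method for PHQ-9 and SF-36 is left open between adjusted and unadjusted tests.

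For recovery, the realistic loss is about 1-6% of variance, or at most about 0.2 percentage points on an SE of 6.9. This assumes a uniform baseline on 17-24, a week-12 SD of 6 and a correlation of 0.2-0.3. The 17% at r = 0.5 is an upper bound that is unlikely to be met. For PHQ-9 and SF-36 the possible loss is larger, 9-35% of variance depending on the correlation (0.3-0.5 assumed) and on which t-test is meant, but it is conditional on the t-test being used. No gain was computed for the 8-12 remission band.

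**What to change.** Change the wording of the Statistical analysis section as follows.

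1. **Recovery rate.** Replace the chi-square test by a logistic model with arm and baseline HAMD-17. Report a standardised risk difference with a delta-method or bootstrap confidence interval, which keeps the comparison on the marginal scale; an adjusted odds ratio would not. Keep the raw percentages as description. Treat the 8-12 remission category in the same way if it is tested.
2. **PHQ-9 and each SF-36 dimension.** Drop the t-test for between-group comparison. Make the covariance analysis already named the deciding method, with the same scale's baseline as a covariate and not as a level of the repeated factor. State that any ANOVA or repeated-measures ANOVA that is kept is supportive.

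No new data, visits or patients are needed. Each model spends one degree of freedom on baseline. The only real cost is some extra analysis work for the standardised interval, which takes a further step after the logistic fit.

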## Discussion

An epidemiological study of people with depression over a 12-month period found that 26.6%, 53.4%, and 20.0% were classified as having mild, moderate, and severe depression, respectively (20). Failure to promptly relieve the depressive state and its accompanying symptoms during early episodes of depression can contribute to its aggravation or recurrence, leading to impaired functioning, reduced productivity, and an increased risk of suicide, which can ultimately result in significant public health and economic consequences (21, 22). The question we put forward in this clinical trial is whether EA is not inferior to ESC for treating mild to moderate first-episode depression. ESC has high efficacy and favorable acceptability in patients with depression in China (23–25). By utilizing an established and effective SSRI as a positive control, we can more precisely evaluate the potential benefits and risks of the novel treatment (EA) in comparison to the standard-of-care therapy (ESC). However, the delayed onset of antidepressant action can prolong patients’ depressive feelings. AEs may also hinder therapeutic effects and result in high dropout rates, which leads to a large proportion of depressed patients who struggle to achieve complete remission and experience relapse. Thus, it is imperative to explore alternative or complementary treatments for depression, particularly in the early phase of the disease (26).

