Traditional Chinese medicine (TCM) theory states that depression is mainly caused by ‘qi’ stagnation, which subsequently leads to the disorder in the brain’s qi systems and an imbalance of yin and yang. In this trial, we will apply a semi-standard point selection consisting of core and additional acupoints, strictly following the syndrome differentiation of TCM theory and allowing some flexibility based on the individual patients’ specific symptoms. The Governor Vessel connects the brain directly and is commonly used to treat depressive disorders (30, 31). GV20 and GV29 are often used to promote the recovery of depressive disorder, as they may facilitate the flow of qi and blood in the brain and restore brain function by ameliorating cognitive deficits (28, 32). The Ren Meridian, has the same origin as the Governor Vessel Meridian. RN6 and RN4, together with ST36 and SP6, can supplement the deficiency and drain the excess, tonifying Qi and blood and relaxing the patient (33), thus regulating the somatization symptoms in conjunction with the Governor Vessel as a whole. In addition, based on the clinical experience of many professional acupuncturists and our previous clinical studies (29, 34), the acupoints we applied effectively improved poor minds and relieved depressive symptoms. The long-range effect is also an important factor of acupuncture treatment, and thus we set long enough intervention period and follow-up period. It will be possible to investigate the enduring effects of acupuncture on depression and ascertain the duration of the therapeutic effect. However, there are still several challenges and limitations in this study. Firstly, it is not feasible to achieve blinding of the acupuncturists during the intervention period, and thus rigorous training will be provided to minimize any potential bias. Acupuncturists will not be involved in either assessing patients or the analysis. Secondly, we are concerned that the initial clinical dose of ESC (10mg) was not effective in relieving depressive symptoms in some patients and therefore allowed them to increase the dose (up to 20 mg) according to their symptoms under the guidance of their psychiatrists. Increasing the drug dose may provide more effective clinical benefits to patients, but at the same time, we cannot be sure whether the changes brought about by the dose of the drug are due to purely time effects or a cumulative dose effect. Thirdly, the outcome of this study was subjective and vulnerable to reporting bias. Further studies should focus on precise objective outcome assessment. Finally, we set a 12-week follow-up time, which may lead to an increased dropout rate. Therefore, more flexible approaches should be employed during the follow-up period, such as making online inquiries or evaluating by phone.

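### Repeated-measures ANOVA over visits turns the PHQ-9 and SF-36 comparisons into complete-case analyses, which does not match the stated intention-to-treat set

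*Protocol article*

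**What the plan says.** All of the following is in the protocol article.

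- **Analysis set** (Statistical analysis): the intention-to-treat population is made up of eligible participants who "have received the intervention at least once, and have provided at least one outcome assessment".
- **Missing data** (same section): "any missing primary outcome data will be replaced by the last observed data point". No rule is given for any other outcome.
- **Method over visits** (same section): "Repeated-measurement analysis of variance was used to compare groups at multiple observation points". The sentence names no outcome.
- **Other between-group methods** (same section): among them, "The student’s t-test will be utilized for comparing measurement data between two groups from baseline to the 6-month follow-up". Analysis of covariance and the Mann-Whitney test are also listed.
- **Software** (same section): "Data analysis for this study will be performed using the statistical software SPSS V.24.0".
- **Visits** (Secondary outcome): for PHQ-9, "This outcome data will be collected at baseline, during the treatment phase (at 4, 8, and 12 weeks) and at the 16-, 24-, and 36-week" visits, which makes baseline plus six. SF-36 is collected at baseline and weeks 4, 8 and 12.
- **Dropout**: the sample size section allows 20%. On antidepressants in general, the Discussion says "AEs may also hinder therapeutic effects and result in high dropout rates". On the length of this trial's follow-up it says "which may lead to an increased dropout rate".

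The abstract also promises that the article will set out the analysis plan for primary and secondary outcomes in full.

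**The concern.** The stated population and the stated method do not fit together. A patient with a single assessment belongs to the intention-to-treat set, yet classical repeated-measures ANOVA (the repeated-measures general linear model in SPSS) removes anyone with a gap at any visit. HAMD-17, PHQ-9 and SF-36 are the only scales collected at several visits, and for PHQ-9 and SF-36 nothing fills the gaps. The longitudinal comparison then describes patients who attended everything, not the patients randomised.

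Two things are at stake. Observed data are thrown away: someone who attends up to week 24 and misses week 36 contributes nothing to the PHQ-9 comparison. In addition, complete-case results are unbiased only if the completers are, in effect, a random subset of those randomised. PHQ-9 is the self-rated depression scale and runs to week 36, so it supports part of the article's claim to study lasting effects.

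**Working it through.** **Step 1. The plan's own figure.** The sample size section gives 81 evaluable per group and 20% dropout: 81 / (1 - 0.20) = 101.25, rounded up to 102 per group and 204 in total. This reproduces. The point uses only the dropout rate and the total, not the derivation of the 81.

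**Step 2. Patients left in a repeated-measures ANOVA.** Formula: 204 × (1 - 0.20) × (1 - m)^k, where k is the number of post-baseline visits (PHQ-9: 6; SF-36: 3). The value m is the share of visits missed sporadically by patients who otherwise stay. The documents give no m, so it is an assumption and is shown as a range.

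| m (assumed) | PHQ-9, k = 6 | SF-36, k = 3 |
|---|---|---|
| 0% | 204 × 0.8 = 163 | 163 |
| 2% | 163.2 × 0.98^6 = 145 | 163.2 × 0.98^3 = 154 |
| 5% | 163.2 × 0.95^6 = 120 | 163.2 × 0.95^3 = 140 |
| 10% | 163.2 × 0.90^6 = 87 | 163.2 × 0.90^3 = 119 |

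The article does not say by which visit the 20% is reached. If it is the total to week 36, the SF-36 counts are lower bounds, because some of those patients would still be present at week 12.

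**Step 3. Direction of bias.** This is a simulation with no true difference, 200,000 patients per arm and six post-baseline visits. Assumptions: SD 5 points, within-patient correlation 0.6, dropout after the first post-baseline visit, and a higher score meaning worse. The table gives the difference in completers' means, EA minus escitalopram, so a negative value favours EA.

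| Dropout, EA / escitalopram | Who leaves | Bias (points) |
|---|---|---|
| 20% / 20% | poor responders in EA; at random in escitalopram | -0.86 |
| 20% / 20% | at random in EA; poor responders in escitalopram | +0.87 |
| 30% / 10% | poor responders in both | -0.77 |
| 10% / 30% | poor responders in both | +0.78 |
| 20% / 20% | poor responders in both | -0.04 (about 0) |
| 20% / 20% | at random in both | +0.03 (about 0) |
| 10% / 30% | at random in both | 0.00 |

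In SD units the largest biases are 0.86 / 5 = 0.17 and 0.87 / 5 = 0.17. They arise when one arm loses poor responders and the other loses patients at random, so they also show how far the completers' mean in a single arm is shifted. Within-arm improvement would be overstated by about 0.17 SD under these assumptions, even where both arms shift equally and the between-arm bias cancels.

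**The case against.** **A missing-data rule for secondary outcomes is often left to the full analysis plan.** That is fair as a general rule, and a bare omission would not be a point. Here the article names a method that cannot be applied to the population it names, and its abstract promises full analysis details for the secondary outcomes.

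**The ANOVA sentence names no outcome.** This stands. Applying it to PHQ-9 and SF-36 is an inference from their visit schedules. It may also be meant for HAMD-17, where the replacement rule could fill gaps, although its reach beyond the week-12 primary outcome is not stated.

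**Other listed tests use available cases.** This also stands. Visit-wise t-tests keep everyone observed at that visit. A reader might infer that the whole intention-to-treat analysis becomes a completers analysis. The text does not support that: the primary outcome has its own rule, and only the repeated-measures comparisons lose patients in this way.

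**A reader might infer that the bias favours EA.** That requires poor responders to leave EA while escitalopram patients leave for reasons unrelated to outcome. No section says so. The 20% is a common rate, and the Discussion's remark on adverse events is background about antidepressants. If those leavers were doing poorly, removing them would favour escitalopram. It is equally tempting to compare the simulated bias with the planning difference of 1.1 / 11.5 = 0.10 SD. That figure belongs to HAMD-17 and is no yardstick for PHQ-9.

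**The Discussion proposes online or telephone follow-up.** This could reduce missed visits, especially for a self-rated scale, but it does not change what the ANOVA does with those that remain missing.

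**Conclusion.** The point holds for the repeated-measures comparisons of PHQ-9 and SF-36. As written, these are complete-case analyses that do not match the stated analysis set. The loss that follows from the plan's own 20% dropout is 41 of 204 patients for the full PHQ-9 series (204 - 163). The range of 120-145 remaining rests on an assumed 2-5% of sporadically missed visits.

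The between-arm bias has no fixed sign. It can run either way if dropout is related to outcome and differs by arm, and it is about zero under a shared mechanism or random dropout. The sizes of 0.8-0.9 points depend on the assumed SD of 5, the correlation of 0.6 and the chosen dropout patterns, so they are illustrations and not forecasts. Because these outcomes are secondary, and the week-12 primary result and the visit-wise tests are untouched, this should be corrected but does not threaten the main conclusion.

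**What to change.** For PHQ-9 and SF-36 over visits, replace the repeated-measures ANOVA with a mixed model for repeated measures (the MIXED procedure in SPSS):

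- Use all observed post-baseline visits, without imputation.
- Fit fixed effects for arm, visit, arm-by-visit, baseline score and baseline-by-visit, with an unstructured covariance matrix.
- Report the arm difference with its confidence interval at each visit collected: weeks 4, 8, 12, 16, 24 and 36 for PHQ-9, and weeks 4, 8 and 12 for SF-36.

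Name the outcomes to which the model applies. If it is also used for HAMD-17 over visits, reconcile it with the last-observation rule stated for the primary outcome, so that the two do not give competing treatments of the same missing values.

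The cost is a short change of wording and slightly more programming, with no new data, patients or software. The model relies on data being missing at random, which is itself an assumption but a weaker one than the complete-case ANOVA needs.

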### Design

This is a multi-center, patient-assessor-blinded, randomized, and controlled trial designed to evaluate the efficacy and safety of EA treatment in patients with mild to moderate first-episode depression and to compare the therapeutic effect between EA and ESC.

We will conduct this study at 4 centers, including Shanghai Municipal Hospital of Traditional Chinese Medicine, Shanghai Mental Health Center, Shanghai Pudong New District Nanhui Mental Health Center, and Shanghai Xuhui District Central Hospital. A total of 204 patients who meet the inclusion criteria will be recruited and randomly assigned into either group, receiving EA treatment with placebo drugs or ESC with sham acupuncture (SA) treatment. After a one-week baseline evaluation, participants will enter a nine-month observation period in this trial. Participants will receive the EA or SA treatment three times a week (every other day) for the first 8 weeks and twice a week (every two days) for the final 4 weeks. Participants will be assessed at the following time points: baseline (1 week before treatment), the 1st month of treatment (4 weeks after treatment starts), the 2nd month of treatment (8 weeks after treatment starts), the end of treatment (12 weeks after treatment starts), and follow-up (1 month, 3 months, and 6 months after treatment ends). All participants will complete the self-rated scales to assess their mental state and quality of life (see the detailed trial process in **Figures 1**, **2**). Throughout the trial, we will adhere to the Standards for Reporting Interventions in Clinical Trials of Acupuncture (STRICTA).

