### Intervention

Treatment will last 12 weeks, with 3 sessions per week (usually every other day) for the first 8 weeks, decreasing to 2 per week (usually every two or three days) for the remaining 4 weeks, and the follow-up period will be 6 months. Each participant will be required to wear an eye patch and assume a supine position during each 25-minute session, which will be conducted in a private, tranquil environment. The treatment will be conducted by licensed acupuncturists with at least three years of experience in acupuncture practice. ESC and placebo tablets were identical in appearance and were administered as a morning dose. Participants will record details of the drug dose, duration of dosing, and response to dosing in a case report form (CRF). All drugs in the 7-dose kit will be dispensed once a week at regular intervals by specialized drug dispensers at each center. Patients may receive additional medication once a week if they need it, which will be recorded by the dispenser.

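### The repeated-measures ANOVA names neither its visits nor a week-12 contrast; if all scheduled visits enter, its group effect does not estimate the week-12 difference

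*Protocol article*

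**What the plan says.** The Statistical analysis section gives the method one sentence: "Repeated-measurement analysis of variance was used to compare groups at multiple observation points". It lists no visits and does not say which model term answers the treatment question.

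The visits have to be taken from elsewhere in the article:

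- The Design section places baseline first among the assessment times: "Participants will be assessed at the following time points: baseline (1 week before treatment").
- HAMD-17 is "collected at baseline, during the treatment phase (at 4, 8, and 12 weeks), and at the 16-, 24-, and 36-week follow-ups" (Primary outcome).
- PHQ-9 follows the same schedule, with measurements after baseline "during the treatment phase (at 4, 8, and 12 weeks) and at the 16-, 24-, and 36-week follow-ups" (Secondary outcome).
- SF-36 stops at the end of treatment: it is "collected at baseline, and during the treatment phase (at 4, 8, and 12 weeks") (Secondary outcome).
- Treatment lasts 12 weeks, after which "the follow-up period will be 6 months" (Intervention). Weeks 16, 24 and 36 are therefore off treatment.

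The endpoint itself is fixed: "The primary outcome will be the mean change in HAMD-17 score from baseline to week 12". The Statistical analysis section also names covariance analysis, Student's t-test, analysis of variance and the Mann-Whitney test for comparing groups. It ties none of them to that endpoint.

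**The concern.** A repeated-measures ANOVA with two arms gives two standard tests: a group main effect and a group-by-time interaction. Neither targets week 12 unless a contrast is specified.

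The main effect averages the arm difference over whatever visits enter. Baseline contributes no treatment effect, because the arms are randomised. The follow-up visits describe what remains after treatment stops, which is a different question from the effect at the end of treatment. The Discussion presents the duration of the effect as something to be studied in its own right, and an all-visit average obscures it.

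The direction matters because the hypothesis is that EA is not inferior to ESC. Where the arms differ most at week 12, averaging over visits with smaller differences makes them look more alike. Using baseline as an outcome also means that it does not serve as a covariate in this model.

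**Working it through.** The plan gives no figure of its own for this analysis, so there is none to reproduce. The check is what the group main effect estimates if all scheduled visits enter with complete data.

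**Inputs from the article**

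- HAMD-17 and PHQ-9: K = 7 visits (baseline; weeks 4, 8, 12 on treatment; weeks 16, 24, 36 off treatment).
- SF-36: K = 4 visits (baseline; weeks 4, 8, 12), none off treatment.
- Endpoint: change from baseline to week 12. Let D be the true EA-ESC difference at week 12.

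**Step 1: what the group effect estimates.** With d_k the arm difference at visit k, the group effect is (1/K) × Σ d_k, each visit having equal weight.

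**Step 2: the part due to baseline, which needs no trajectory.** Randomisation makes the expected baseline difference zero. The group effect is therefore (K − 1)/K times the post-baseline average:

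- HAMD-17 and PHQ-9: 6/7 = 0.86
- SF-36: 3/4 = 0.75

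**Step 3: the part that depends on the trajectory.** The article gives no trajectory, so those below are assumptions. Entries are d_k as a fraction of D.

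| Assumed trajectory | Base | 4 | 8 | 12 | 16 | 24 | 36 | Group effect / D |
|---|---|---|---|---|---|---|---|---|
| Linear build-up, gone after treatment | 0 | 1/3 | 2/3 | 1 | 0 | 0 | 0 | 2/7 = 0.29 |
| Linear build-up, linear fade to zero | 0 | 1/3 | 2/3 | 1 | 2/3 | 1/3 | 0 | 3/7 = 0.43 |
| Linear build-up, half retained | 0 | 1/3 | 2/3 | 1 | 1/2 | 1/2 | 1/2 | 3.5/7 = 0.50 |
| Linear build-up, sustained | 0 | 1/3 | 2/3 | 1 | 1 | 1 | 1 | 5/7 = 0.71 |
| Immediate, sustained | 0 | 1 | 1 | 1 | 1 | 1 | 1 | 6/7 = 0.86 |
| Linear build-up, grows to 2 D | 0 | 1/3 | 2/3 | 1 | 4/3 | 5/3 | 2 | 7/7 = 1.00 |

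For scale only, a week-12 difference of 4 points would appear as 4 × 2/7 = 1.1 to 4 × 1.00 = 4.0 points.

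For SF-36, a linear build-up gives (0 + 1/3 + 2/3 + 1)/4 = 0.50 and an immediate effect gives 3/4 = 0.75.

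**Step 4: does dropping baseline suffice?** No. Averaging the six post-baseline visits moves 0.43 to 0.50 (build-up and fade), 0.71 to 0.83 (build-up, sustained) and 0.86 to 1.00 (immediate, sustained). The early and follow-up visits are still mixed with week 12.

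**Step 5: the interaction.** The omnibus group-by-time test has (2 − 1)(K − 1) degrees of freedom: 6 for HAMD-17 and PHQ-9, 3 for SF-36. It tests any departure from parallel profiles and does not isolate week 12. A week-12-minus-baseline contrast in the same model returns D − 0 = D, undiluted, under every trajectory above. The article specifies no such contrast.

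**The case against.** The strongest reply is that the misuse is inferred. The sentence does not say that baseline is a level of the time factor, that all visits enter one model, or that the main effect is the comparison; it could mean comparisons at each visit. The one visit range in that section, "comparing measurement data between two groups from baseline to the 6-month follow-up", belongs to the t-test. This stands, and it is why the point is conditional. A reader might infer that the plan does count baseline as an outcome and does pool on- and off-treatment visits; the text leaves this open without saying so.

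A reader might also conclude that the week-12 difference is cut to about half. That is one case among the assumed trajectories. Only the 6/7 and 3/4 factors are general, and they apply to the post-baseline average, not to the week-12 difference.

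A third tempting reading is that the non-inferiority conclusion is biased. The article does not support it: the ANOVA is not assigned to the week-12 change, the margin is not attached to it, and covariance analysis is also listed (without its covariate).

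It can further be said that visits and model terms belong in a full analysis plan. That has some weight, but the Abstract says this article describes the analysis plan for primary and secondary outcomes in full. The method is also named here as a between-group comparison without the contrast it needs.

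**Conclusion.** The point holds in conditional form. If all scheduled visits enter the repeated-measures ANOVA, its group main effect does not estimate the week-12 change and can understate the week-12 difference. Under the assumed trajectories it is about 0.3 to 1.0 of that difference, reaching 1.0 only if the difference doubles after treatment ends. This range assumes complete data and equal visit weights. It is not a bound, since the difference could also change sign during follow-up. For SF-36 only baseline and the earlier treatment visits dilute the effect, as there is no off-treatment visit.

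The direct consequence is for the longitudinal and secondary comparisons. Harm to the non-inferiority conclusion is a risk if this effect were read as evidence of similarity; it is not shown. The sentence should be changed, because a clearer analysis can be had from the same data.

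**What to change.** In the Statistical analysis section, replace the repeated-measures ANOVA sentence with a model that has:

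- post-baseline visits only as outcomes;
- the baseline score of the same scale as covariate;
- treatment, visit and treatment-by-visit terms.

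Report the EA-ESC difference with its confidence interval at each visit. Name week 12 as the contrast that carries the treatment comparison. For HAMD-17 and PHQ-9, report weeks 16, 24 and 36 separately as off-treatment results. State that no conclusion will be drawn from a group effect averaged over all visits.

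The cost is a few lines of text, with no new data, visits or patients. The single all-visit p-value is lost.
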